## Abstract

**Background:**

Proximal humerus fractures (PHF) are common in adults above 50 years, often following low-energy trauma and underlying osteoporosis. Randomized trials in patients 60 years and older have found no clinically important difference in 1- and 2-year outcomes between surgical and non-surgical treatments. There is limited evidence for the 50–65 age group, who may have different functional demands and even a different overall health status. There is limited knowledge to guide treatment decisions for this age group.

**Method:**

A multicenter, parallel-group, randomized, superiority trial comparing osteosynthesis with non-surgical treatment in patients aged 50–65 years with displaced PHF. A total of 60 patients will be randomized equally to surgical treatment (primary osteosynthesis) or non-surgical treatment. Follow-up visits are arranged at 6 weeks and 6 months for all patients, with an additional 12-week visit mandatory for the surgical group and optional for the non-surgical group. The primary outcome is the between-group difference in Oxford Shoulder Score at 12 months. Sample size was calculated assuming a clinically relevant difference of 9.6 points on the OSS (SD 12), corresponding to 80% power at a 5% significance level. In case of treatment failure (persistent pain or a failed osteosynthesis), a salvage procedure will be offered. Patients not consenting to randomization will be asked to participate in a non-randomized cohort. They will have baseline data and preferences recorded, and they will receive the same follow-up and outcome assessments.

**Discussion:**

Young shoulder CARE trial aims to provide insights into the treatment of displaced proximal humerus fractures in patients aged 50–65 years, and to understand the benefits and harms of both surgical and non-surgical treatment options. The trial results will be published in an open-access peer-reviewed journal.

**Trial registration:**

Clinicaltrials.gov, NCT06416618, registered 14 May 2024.

**Supplementary Information:**

The online version contains supplementary material available at 10.1186/s13063-025-09283-x.

## Background

Proximal humerus fractures (PHF) are common injuries with an incidence of 138 per 100,000 person-years in adults aged 18 years and above in Denmark, increasing with age and have remained stable over decades [1]. In Denmark (2018), the total annual number of PHF was 6318 (72% women) [1]. In Finland (2019), the incidence among individuals aged over 16 years was 105 per 100,000. The incidence was higher in females and increased with age, particularly among those aged 50 years and older. The total annual number in 2019 was 4826 cases [2]. Less than half of the fractures are minimally displaced [3, 4], with displaced fractures defined as at least one of Codman’s four anatomic segments being displaced by ≥ 1 cm or angulated ≥ 45° (as defined by Neer [5]).

Meta-analyses comparing surgical and non-surgical treatments for PHF have been rated as having critically low methodological quality [6]. A Cochrane review reported high‐certainty evidence of no clinically important difference between surgical and non‐surgical treatment in patient‐reported shoulder function 1 and 2 years after injury [7]. Most included studies focus on older patients; however, a subgroup analysis (aged 16–65) from the ProFHER study [8] found no statistically significant differences in patient-reported shoulder function (Oxford Shoulder Score (OSS)) between surgical and non-surgical treatment at 6 months, 1 year, and 2 years. There was a trend toward more rapid improvement among younger patients (< 65 years) in the non-surgical group compared to those in the surgical group.

This study focuses on patients aged 50–65. Individuals in this age group often differ from older adults in terms of functional demands, work status, activity level, overall health, and rehabilitation expectations. PHF is uncommon in patients below the age of 50, whereas incidence increases markedly from this age and onward [1, 2]. More than 80% of the fractures occurred in patients above 50 years [6], in females [1, 2, 9] and results from low-energy trauma [3, 9]. Around this age, hormonal and metabolic changes begin to influence bone quality turnover [10] and may effect fracture healing [11]. Stratification by sex reveals a female predominance from the age of 50 [1, 2, 6], which coincides with an increase in age-related decrease of bone mineral density [10]. The exact prevalence of osteoporosis in the general population is not precisely known, as detection often relies on bone mineral density measurements, which are not routinely performed. Reduced bone mineral density is a known risk factor for complications following osteosynthesis [12].

The surgical treatment of choice for displaced PHF in adults 50–65 years is anatomical reduction followed by osteosynthesis if possible [13–15]. Surgical options include internal fixation with locking plates, intramedullary nails or joint replacement with hemiarthroplasty, or reverse shoulder arthroplasty. Complication and reoperation rates are high after surgery [16].

Orthopedic surgeons may encounter challenges in making treatment decisions with patients in this specific age group, as existing randomized trials have predominantly focused on older individuals [17]. There is an intermediate age group of patients for whom it remains uncertain whether surgical intervention is superior to non-surgical management in terms of benefits and harms.

The aim of this study is to assess whether osteosynthesis results in superior patient-reported shoulder function compared to non-surgical treatment, as measured by the Oxford Shoulder Score at 12 months, in patients aged 50 to 65 years with displaced proximal humerus fractures.

We hypothesize that surgical treatment with osteosynthesis results in superior patient-reported shoulder function, measured by the Oxford Shoulder Score at 12 months, compared to non-surgical management in patients aged 50–65 years with displaced proximal humerus fractures. Accordingly, the null hypothesis states that shoulder function, measured by the Oxford Shoulder Score, is not superior following surgical compared to non-surgical treatment.

## Methods: patients, intervention, and outcomes

### Study design

The study is a two-center, parallel-group, randomized, superiority trial comparing osteosynthesis with non-surgical treatment following a displaced PHF in patients aged 50–65 years with a 1:1 allocation ratio.

The protocol will follow the PREPARE trial guide [18] and the SPIRIT checklist [19]. PRECIS-2 assessment indicates that the trial is pragmatic with 42 points out of 45 points (see Supplementary information, file 1) [20]. The study will be reported according to the CONSORT checklist [21]. The statistical analysis plan (Supplementary information, file 2) will follow the Guidelines for the Content of Statistical Analysis Plans in Clinical Trials [22]. All checklists are available in Supplementary information, file 3.

The trial flow and timeline for data collection are outlined in Fig. 1 and Table 1.

**Fig. 1 Fig1:**
[figure not shown]
Trial flowchart

**Table 1 Tab1:** Timeline and overview of enrolment, intervention and assessments

		Study period							
	Enrolment	Allocation	Post-allocation						Close-out
Timepoint	Pre-randomization	Randomization	Day of intervention (2 weeks post-injury)	Week 2^a^	Week 6^a^	Week 12^a^	6 months^b^	12 months^b^	24 months ^b^
Enrolment									
Eligibility screen	x								
Informed consent	x								
Allocation		x							
Intervention									
Surgical treatment			x						
Non-surgical treatment			x						
Assessments									
Radiographs, surgery	x		x	x		x	x		
Clinical control surgery			x	x		x	x		
Radiographs, non-surgical	x		x		x	(x)^c^	x		
Clinical control, non-surgical			x		x	(x)^c^	x		
Referred to DXA-scan			x						
OSS							x	x	x
EQ-5D-3L							x	x	x

^a^For surgery-group, number of weeks after surgery. For the non-surgical group, number of weeks after injury

^b^Number of months post injury, regardless of group

^c^Possible additional control

### Participants

Patients will be recruited from the orthopedic departments at Zealand University Hospital in Denmark and Tampere University Hospital in Finland.

The following inclusion criteria will apply:Patients aged between 50 and 65 years with a displaced proximal humerus fracture after a low-energy trauma.Patients should be cognitively capable of answering the follow-up questionnaires.

The following exclusion criteria will apply:

Communication:The patient does not understand written and spoken native language (Danish or Finnish)Inability to give informed consent

Fracture criteria:Fractures assessed to be non-reconstructable by the treating surgeonIsolated tuberosity fracture, fracture dislocations, open fractures, and fractures with involvement of the articular surfaceLess than 25% contact between the humeral head and humeral shaft measured at two perpendicular radiographs at 2 weeks postinjuryPathological fractures or previous fractures in the same proximal humerusConcomitant fractures, which could influence the outcome

Other criteria:

Paralysis of the upper extremity

### Recruitment

Patients admitted to the emergency department will be clinically examined by the emergency doctor. Two perpendicular plain radiographs will be obtained. If a displaced PHF is diagnosed, the patient will be referred to the outpatient clinic within 2 weeks postinjury. Patients will be screened for eligibility based on the initial radiographs and medical records by the investigator at the clinic. During the first visit to the outpatient clinic, the patient will be informed about the study. Potential participants will receive verbal and written information about the study from the local investigator. If eligible and consenting to participate, the local investigator will provide face-to-face trial instructions, and informed consent will be obtained.

### Non-randomized cohort

Eligible patients who decline participation will be recorded; when possible, their reasons for declining will be noted. These patients will be invited to participate in the non-randomized cohort. The patient can choose surgery only if recommended by the surgeon; such cases will be reported. Patients in the non-randomized cohort who provide informed consent will participate in the same treatment, rehabilitation, follow-up, and outcome assessments as the randomized cohort, with data recorded for research purposes.

### Randomization and concealment of allocation

We will use Research Electronic Data Capture (REDCap) [23] to generate an irreversible randomization sequence. A person not involved in the project will generate and upload the allocation table using “R.” All investigators will be blinded to the allocation table. The person not involved in the project will have no access, including no access to the data. We will be using block randomization with varying block sizes of 4 and 6, stratified by location. REDCap will conceal the sequence for the investigators before allocation takes place. Enrolment and allocation will occur on-site by LH, AL, BS, or LK. A REDCap built-in functionality ensures that only patients who meet all inclusion and no exclusion criteria can be randomized.

### Intervention

All patients will receive standard pain management following local guidelines and will be provided with a sling and swathe on the day of the injury in the emergency room. After 10 to 14 days, all patients will undergo evaluation in the outpatient clinic.

#### Surgical group

The surgical group will receive osteosynthesis with a locking plate (Philos System, J&J DePuy Synthes) or an intramedullary locking nail (Multiloc Humeral Nail, J&J DePuy Synthes), according to the surgeon’s preference. The patients will be provided with a sling and swathe immediately after the surgery. From the first postoperative day, only the sling will be used. Two weeks postoperatively, patients will undergo clinical and radiological follow-up in the outpatient clinic. At 12 weeks postoperatively, patients will have another clinical and radiological follow-up. This is the current standard care for surgical treatment with a plate or intramedullary nail. All surgeries in this study will be performed by specialized upper limb trauma or shoulder surgeons, each with a minimum of 5 years of subspecialty experience.

#### Non-surgical group

Patients in the non-surgical group will be offered an optional sling for comfort for an additional 1–2 weeks at their first visit, 10–14 days post-injury. At week 6 post-injury, all patients will undergo clinical and radiological follow-up. This represents the current standard care for non-surgical treatment of displaced PHF at the departments.

If there is still severe pain at week 6, it is considered a treatment failure. Severe pain is defined as being unable to sleep due to pain and/or requiring opioids to manage it (without opioid use prior to injury). If there is little progress but moderate pain, an additional consultation can be provided 12 weeks post-injury with clinical and radiological follow-up.

#### Both groups

Patients will be offered standard 6-month radiographs and clinical assessments, as well as a diagnostic workup for osteoporosis with a DXA scan. Osteopenia is defined as a *T*-score between − 2.5 and − 1. Osteoporosis is defined as a *T*-score lower than or equal to − 2.5 [24]. Additionally, osteoporosis can be diagnosed by hip and spine fractures, which, in Denmark, is considered pathognomonic for osteoporosis.

Boths groups will be referred to rehabilitation in the municipalities. An overview of the rehabilitation timeline is presented in Table 2. Patient information sheets are provided in Supplementary file 4. The rehabilitation program is similar, starting post-surgery for the surgical group and from the time of injury for the non-surgical group. The duration, intensity, and exercises used will be tailored in collaboration between the patients and the physiotherapist. Rehabilitation typically lasts 6–12 weeks. Adherence to rehabilitation is defined as completing at least 6 weeks of rehabilitation and following rehabilitation protocol.

**Table 2 Tab2:** Rehabilitation timeline for surgical, non-surgical, and salvage groups

Group	Weeks after operation/injury	Rehabilitation activities
Surgical group	Week 0–6	Free hand, wrist, elbow, and cervical movement in a full range of motion daily is advised. Free movement exercises with a maximum of 1 kg load. Avoid outward rotation beyond the neutral position and no inward rotation corresponding to the hand behind the back. We recommend using the arm for daily activities as soon as the pain allows. Passive movement with a focus on mobility and gradually additional focus on active movement
	Week 6–12	Free movement exercises with gradually increased load
	From week 12	Full load allowed
Non-surgical group	Week 0–2	Sling and swathe worn at all times
	Week 2–6	Begin pendulum exercises with circles in and out. Free movement exercises except outward rotation beyond neutral position and no inward rotation corresponding to the hand behind the back. We recommend using the arm for daily activities as soon as the pain allows. Passive movement with a focus on mobility and gradually additional focus on active movement
	Week 6–12	Free movement exercises with gradually increased load
	From week 12	Full load allowed
Salvage procedure	Week 0–6	Free hand, wrist, elbow, and cervical movement in a full range of motion daily is advised. Free movement exercises with a maximum of 1 kg load. Avoid outward rotation beyond the neutral position and no inward rotation corresponding to the hand behind the back. We recommend using the arm for daily activities as soon as the pain allows. Passive movement with a focus on mobility and gradually additional focus on active movement
	Week 6–12	Free movement exercises with gradually increased load
	From week 12	Heavier load allowed (max. 15 kg/35 lbs lifelong)

#### Treatment failure

In case of treatment failure in either group, defined as persistent pain or a failed osteosynthesis, a salvage procedure with secondary osteosynthesis, including the possibility to use a locking plate with a graft or a reverse shoulder arthroplasty (RSA), will be offered. The decision to proceed to a salvage procedure will be made in collaboration with the patient and the surgeon. Failed osteosynthesis and the most appropriate salvage procedure will be defined by the surgeon.

Cross-over to RSA or revision osteosynthesis is considered a failure of treatment regardless of group allocation. The patient will remain in the study. The reason for crossing over will be noted and reported.

### Strategies to improve retention

Patients will receive a phone number to contact the local investigator with any questions. All included patients will be seen by either LH, SB, AL, BS, or LK at all appointments. Follow-up is planned at 6, 12, and 24 months. The 6-month follow-up includes radiographs, clinical assessment (range of motion, strength, and test for subacromial pain) and questionnaires. Data will be stored using Research Electronic Data Capture (REDCap) [23]. At the 12- and 24-month follow-ups, questionnaires will be automatically sent by REDCap for patients to complete from home, provided the patient has a mailing address. Patients are asked to accept telephone calls if they miss follow-up visits to promote patient retention and complete follow-up. Reminders will be sent 2 and 4 weeks after receiving their 12- and 24-month questionnaires. After 6 weeks, completion by phone will be offered if still unanswered [25].

### Outcome

The primary outcome will be the OSS at 12-months. The secondary outcome will be OSS at 6- and 24-month and EQ-5D-3L score measured at the 6, 12, and 24 months. Secondary outcomes will include the incidence of adverse events in all groups and the rate of conversion to surgery in nonoperative group.

#### Oxford Shoulder Score

OSS is a patient-reported shoulder-specific outcome measure to assess shoulder function. It consists of 12 questions on a 5-point Likert scale (both pain- and function-related), each offering five ordinal response options. The cumulative score ranges between 0 and 48, being 0 (worst) to 48 (best, no pain, or functional limitation). The questionnaire includes a mix of functional ability and pain-related questions. It is validated in adults with shoulder pain from a degenerative or inflammatory condition (median age 57.4 in the UK) [26], and in Denmark in patients with post-traumatic shoulder diseases, including impingement and sequelae after PHF [27]. Patients in follow-up cohorts do not need to attend the clinic in person to complete the OSS [27].

#### Quality of life

EQ-5D-3L is a generic health-related quality-of-life assessment tool validated as a quality-of-life measure in patients with PHF [28]. It consists of a 5-dimension descriptive questionnaire about mobility, self-care, usual activities, pain/discomfort, and anxiety/depression as a measure for health-related quality of life [29]. Each dimension has 3 levels: no problems, some/moderate problems, and unable/extreme problems. Each dimension is weighted differently and results in a total score based on the EQ-5D index calculator (TTO). The EQ-5D-3L also includes an overall scale (numeric rating scale) in which patient rates their overall health condition today on a scale between 1 and 100, with 100 being the highest level of health imaginable.

#### Adverse events

Serious adverse events, as defined by the WHO [30], will be reported to a data monitoring committee (DMC). These events are defined as those leading to death, being life-threatening, requiring inpatient hospitalization, or necessitating reoperation.

Other adverse events, whether surgical or non-surgical related, will also be reported.

Systematic reviews on terms and definitions for complications after surgical [31] and non-surgical treatment [32] have been conducted. Based on international consensus on the core event set for PHF, both surgical and non-surgical treatments, eight event groups are defined [33]. The following adverse event groups will be monitored: implant, osteochondral, shoulder instability, peripheral neurology, vascular, infection, device, superficial soft tissue, and deep soft tissue. In addition to this, we have chosen to monitor clinical symptoms such as persistent severe pain. The event groups are elucidated in Supplementary information, file 5 – Complications.

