#### Interim analyses

An interim analysis will be conducted when 50% (*n* = 30) of the randomized patients have completed their 6-month follow-up, focusing on OSS, failure to treatment, and serious complications. A third party will blind the data to treatment location before analysis. Regardless of whether the interim analyses suggest that the study is unlikely to achieve its primary objectives, the study will proceed as initially planned.

A DMC has been organized to monitor and evaluate the data from the interim analysis. The DMC consists of five independent members: two orthopedic researchers and an orthopedic nurse from Denmark, and one orthopedic researchers and one orthopedic nurse from Finland. All members have equal standing within the committee.

The DMC will monitor unexpected, unwanted events; continued inclusion will be considered if the failure rate is above 30%. Intervention-related hospitalization or mortality will be reported to the ethics committee.

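### The serious-adverse-event criteria leave out lasting disability and prolonged stay, and 'reoperation' fits only a shoulder already operated on, so similar harms are graded differently

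*Protocol article*

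**What the plan says.** The Adverse events section of the protocol article cites a WHO source for seriousness and then prints its own list: "leading to death, being life-threatening, requiring inpatient hospitalization, or necessitating reoperation". Events meeting the list go to the DMC. For the rest it says: "Other adverse events, whether surgical or non-surgical related, will also be reported". It also names the event groups to be monitored: "implant, osteochondral, shoulder instability, peripheral neurology, vascular, infection, device, superficial soft tissue, and deep soft tissue". Symptoms are added to these: "In addition to this, we have chosen to monitor clinical symptoms such as persistent severe pain".

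Later surgery is described in other sections under other names:

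- Treatment failure covers both arms ("In case of treatment failure in either group, defined as persistent pain or a failed osteosynthesis, a salvage procedure"), and "Cross-over to RSA or revision osteosynthesis is considered a failure of treatment regardless of group allocation".
- The Outcome and Conversion to surgery sections call a first operation in a non-surgical patient a conversion. Its rate is a secondary outcome.
- The Salvage procedure section calls hardware removal a reoperation and classes it as a complication, not as salvage.

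The Interim analyses section has the interim look cover the Oxford Shoulder Score, treatment failure and serious complications, with the DMC evaluating the result. It does not tie 'serious complications' to the list in the Adverse events section.

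**The concern.** The printed list is closed: it says what serious events are, not what they include. Two kinds of harm fall outside it. One is an event that leaves lasting disability but leads to no admission or further surgery. Peripheral neurology is a monitored group, so the protocol itself expects nerve injury. The other is a complication that keeps an admitted patient in hospital longer; it does not require hospitalization, because the patient is already there.

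The fourth criterion is also tied to treatment history. A shoulder can be reoperated on only if it has been operated on before. Every patient treated as allocated in the surgical arm is exposed to this criterion from the first operation. A patient in the non-surgical arm is exposed only after a conversion, and the conversion itself does not meet it.

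At stake is whether the serious label means the same thing in both arms. It decides which individual events the Adverse events section commits to send to the DMC, and it probably governs one of the three interim items. In a small, unblinded comparison of surgery with no surgery, a label that depends on the route of treatment makes that part of the harm picture hard to read.

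**Working it through.** **Figures available.** The documents give no rate for any adverse event, so no stated figure on this point can be reproduced. The only relevant number is the arm size. Inputs from Sample size and power considerations: difference 9.6, SD 12, 80% power, 5% level, 15% loss. With a two-sided normal approximation, n = 2 × (1.960 + 0.842)² × (12/9.6)² = 2 × 7.85 × 1.5625 = 24.5, so 25 per group; 25/0.85 = 29.4, so 30. The stated 25 and 30 are reproduced, and the point here does not affect them.

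**Applying the printed criteria to concrete cases.**

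| Event | Meets a printed criterion? | Other route in the protocol |
|---|---|---|
| Permanent nerve deficit, no admission, no reoperation (either arm) | No | Other adverse event, peripheral neurology group |
| Complication that only lengthens an inpatient index stay | No | Other adverse event |
| Day-case hardware removal | Yes, reoperation | Complication |
| Day-case first operation after failed non-surgical treatment | No | Treatment failure; conversion rate; salvage analysis |
| Same first operation with admission | Yes, hospitalization | As above |
| Further operation after a conversion | Yes, reoperation | Salvage or complication |

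Rows three and four show the unevenness. Both are unplanned day-case operations on the injured shoulder, and only the one on an already operated shoulder is serious. The last row shows that the criterion follows the operated shoulder, not strictly the allocated arm.

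**Direction.** Leaving out prolonged stay can lower the serious count only among operated patients. The reoperation wording can raise the count in the surgical arm relative to the non-surgical arm. The two pull in opposite directions, so the net effect cannot be signed from the documents.

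**Size.** One reclassified patient changes an arm's serious-event rate by 1/30 = 3.3 percentage points. At the interim look (30 patients, 1:1 allocation, so about 15 per arm) it is about 1/15 = 6.7 points.

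**Illustration on assumptions only.** Suppose 10% of each arm has an unplanned shoulder operation: 0.10 × 30 = 3 per arm. All 3 in the surgical arm are reoperations and count as serious. In the non-surgical arm the number counted depends on the share of conversions that are admitted:

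- 0% admitted: 3 × 0 = 0, so 3 v 0
- 50% admitted: 3 × 0.5 = 1.5, so 3 v 1.5
- 100% admitted: 3 × 1 = 3, so 3 v 3

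The documents do not say whether conversions are inpatient, so the imbalance from this criterion runs from 3 patients to none.

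**The case against.** The strongest reply is that little is lost. The DMC is not confined to the four criteria: it also evaluates treatment failure, considers continued inclusion if the failure rate exceeds 30%, and watches for unexpected, unwanted events. Failure is defined for either group, so a non-surgical patient who goes on to salvage reaches the DMC by that route. All adverse events are a secondary outcome and are reported descriptively, so a nerve palsy is counted whatever its label. No test of serious-event rates between arms is planned. If conversions are inpatient, the hospitalization criterion catches them and the reoperation imbalance disappears. The WHO source and the supplementary file on complications are not shown and may say more.

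Most of this stands, and it limits the point. A reader might infer that these harms go unrecorded or that the DMC never learns of conversions; the sections on adverse events, treatment failure and interim analyses show otherwise. It does not dispose of the point. The failure route carries neither a lasting nerve deficit nor a prolonged stay. The article prints its own closed definition, and the supplementary file is cited there for the event groups, not for seriousness. Whether the list departs from the WHO source cannot be checked and is not relied on.

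A reader might also extend the criticism to the ethics committee, because "Intervention-related hospitalization or mortality will be reported to the ethics committee". That trigger is separate and does not mention reoperation, so the wording at issue cannot make that committee's view uneven by arm. Reading it as a duty to report every planned admission for the allocated operation is strained: the sentence follows one on unexpected, unwanted events, and a planned admission is neither. How much more that committee should receive is a matter of policy, not an error in the text.

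**Conclusion.** The point holds as a defect of classification. Read as printed, the definition grades a lasting disability or a prolonged stay as non-serious, and it grades unplanned shoulder operations by whether there was an earlier operation. The effect is confined to the serious label and the serious-event reporting to the DMC. Capture of events, the primary outcome, the sample size and the planned efficacy comparisons are untouched.

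The only size the documents support is 3.3 percentage points per reclassified patient on 30 per arm. It is tempting to put a number on the events missed, but with no rates given any total would be assumed. The conclusion rests on reading the four criteria as the complete list. The reoperation imbalance further assumes that some conversions are done without admission, and the prolonged-stay gap assumes that at least some index operations are inpatient; the documents settle neither.

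**What to change.** In the Adverse events section:

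- Add two criteria: the event prolongs an existing hospital stay, or it results in persistent or significant disability.
- Replace the reoperation criterion with: necessitating an unplanned operation on the injured shoulder, in either arm. This covers conversions and hardware removal alike.
- State that admission for the allocated initial operation is not itself an event.

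In the Interim analyses section, say that 'serious complications' uses this same definition.

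The cost is the wording of one definition and one cross-reference, with matching options in the REDCap form. A few more events will count as serious. Treatment, sample size and the efficacy analysis do not change.
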